## Methods: participants, interventions, and outcomes

### Study setting {9}

In Finland, over 99% of all pregnancies are monitored in Healthy Maternity Clinics [63] that are part of the basic healthcare arranged by the municipalities. The clinics provide screening for fetal chromosomal abnormalities at the end of the first trimester and for severe structural abnormalities between 19 and 21 gwks, as well as offer family support, with attention to relationships and parenting. Risk pregnancies are also referred to maternity outpatient clinics in hospitals. Deliveries and conditions requiring emergency care are treated in hospitals as well. The Finnish health care system supports women experiencing miscarriage, stillbirth, or adverse pregnancy outcomes [64]. The perinatal mortality rate in Finland was 0.4% in 2019 [65].

This study is carried out at the Hospital District of Southwest Finland, at the maternity clinic of Turku University Hospital, and in collaboration with the Department of Psychology, University of Turku. This tertiary level hospital offers extensive specialized health care services to the residents. There are approximately 4000 births annually; in 2020, there were 3811 births [66].

### Eligibility criteria {10}

The inclusion criteria are as follows:(1) 10–15 points on the EPDS, (2) singleton pregnancy, (3) over 18 years of age, (4) body mass index under 35, and (4) fluency in the Finnish language.

The exclusion criteria are psychotic and self-destructive symptoms. The use of antidepressant medication is not an obstacle to participation.

The women are recruited after the routine screening for severe structural abnormalities between 19 and 21 gwks offered by the municipalities. Severe structural abnormalities are an exclusion criterion.

### Who will take informed consent? {26a}

An information letter, which can be found on the project’s webpage is emailed to the women who have completed the depression screener through the webpage. The graduate students in psychology collect the informed consent forms from the participants at the beginning of the first study visit, which is the attachment representation interview.

### Additional consent provisions for collection and use of participant data and biological specimens {26b}

These are not applicable. No biological specimens are collected in this study.

## Interventions

### Explanation for the choice of comparators {6b}

The Finnish Institution for Health and Welfare (THL) recommends that the Healthy Mother Clinics screen for depressive symptoms using EPDS at 13-18 gwks. If the EPDS score is 13 or more, THL recommends that the pregnant woman should be referred to the general practitioner in a Healthy Mother Clinics for further assessment. If the total score is 10–12 points, the EPDS should be repeated within 2-4 weeks. In case of self-destructive thoughts, immediate help should be organized, also on call [67]. All the pregnant women are screened for depressive symptoms using the EPDS in the communal Healthy Mother Clinics. The pregnant woman’s mood should also be assessed by observation and discussion [68].

### Intervention description {11a}

The method is pregnancy ultrasound combined with an interactive approach; a joint observation of the fetus based on the woman’s wishes. An obstetrician, a specialist in maternal-fetal medicine, and a psychologist specialized in psychotherapy and infant mental health jointly conduct the intervention. Three intervention visits are carried out between 25 and 33 gwks because the visibility of the fetus decreases after 33 gwks.

The focus of the ultrasound examination is to follow the fetal activities inside the womb, to work with mental images regarding the fetus and the pregnancy, and listen to the woman expressing her thoughts regarding the fetus. In the beginning, the obstetrician ensures that the pregnant woman understands the images on the screen. Thereafter, the obstetrician, the psychologist, and the woman jointly watch what the fetus does during the examination. Observations are made on what is seen on the screen and on fetal activities taking into account the woman’s reactions. The sonographer and the psychologist avoid making any interpretations about the fetus or its behavior. Rather, they comment on the behavior as it is happening. The aims are to facilitate and emphasize pregnant women’s own perceptions of the fetus. With 4D ultrasound, it is possible to see the fetus’ face and facial expressions and discuss these with the mother. The intervention visits follow a structured course (Appendix 2. The course of intervention visits). The examination lasts approximately 40 min, and the women participate alone without the presence of the fetus’ father. The ultrasound examinations are videotaped for later analysis.

The other parent may join the ultrasound examination once after the actual intervention to see the fetus.

### Criteria for discontinuing or modifying allocated interventions {11b}

No modifications have been made so far. All participants receive the same intervention treatment; three interactive ultrasound examinations lasting approximately 40 min each. In case of a pregnancy complication, the woman is referred to a clinical check-up. Also, in case of fetal demise, an obstetrician is contacted immediately. Interactive ultrasound examinations are conducted in the same outpatient clinic where risk pregnancies are monitored. The obstetricians, who are specialists in maternal-fetal medicine are also employees of the women’s clinic in Turku University Hospital.

### Strategies to improve adherence to interventions {11c}

The three intervention teams each comprise a psychologist and an obstetrician. All interventionists receive training in the interactive approach. The structure of each session is described, and key themes of the sessions are listed. Intervention teams meet together frequently to review the video-recorded intervention sessions in order to enhance adherence to the course of the intervention visits.

### Relevant concomitant care permitted or prohibited during the trial {11d}

Prenatal care continues as usual. Other support or therapeutic treatments are also allowed.

### Provisions for post-trial care {30}

No provisions for post-trial care are necessary.

### Outcomes {12}

The primary outcome of the study is perinatal depressive symptoms analyzed as a change in the EPDS- mean score from before the intervention to after the intervention, maternal attachment, and prenatal representations before and after the intervention. The secondary outcomes are maternal-infant-relationship- related outcomes; maternal pregnancy-related psychological distress, and mother-infant interaction. The secondary outcomes are analyzed with both quantitative and qualitative methods.

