**Methods:**

A controlled randomized setting was designed to assess whether interactive 4D-ultrasound intervention would decrease maternal depressive symptoms, strengthen maternal-fetal attachment, and mother-infant relationship. An obstetrician and a psychologist specialized in infant mental health conduct the interventions. The focus is to jointly observe the behavior of the fetus according to the mothers’ wishes. Altogether, 100 women scoring 10–15 on Edinburgh Pre-/Postnatal Depression Scale (EPDS) and with singleton pregnancy are recruited using a web-based questionnaire. Half of the participants will be randomized to the intervention group and will undergo three interactive ultrasound examinations. The primary outcomes are a decrease in perinatal depressive symptoms assessed with EPDS and an increase in maternal attachment. The maternal attachment was assessed using the Working Model of the Child Interview (WMCI), the Maternal Antenatal Attachment Scale (MAAS), and the Maternal Postnatal Attachment Scale (MPAS). Secondly, we hypothesize that if the intervention decreases prenatal depressive symptoms and improves prenatal attachment, the decrease in depressive symptoms and improvement in mother-infant relationship is seen postnatally.

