### Objectives {7}

#### Aim

The primary aim of the present study is to evaluate, whether interactive ultrasound decreases perinatal depressive symptoms by increasing maternal attachment. The secondary aim is to evaluate whether interactive ultrasound improves also postnatal mother-infant interaction.

The specific hypotheses are as follows:
The intervention decreases prenatal depressive symptoms and improves the attachment to the fetus.
The mothers in the intervention group will have fewer depressive symptoms after intervention than before the intervention.The decrease in depressive symptoms will be greater in the intervention group than in the control group.The improvement of prenatal attachment from the pre-intervention to the post-intervention time will be greater in the intervention group compared with the control group.The mothers in the intervention group will have a more balanced attachment representation after the intervention than before the intervention.The change from non- balanced to balanced attachment representations will be greater in the intervention group than in the control group.If the intervention decreases prenatal depressive symptoms and improves prenatal attachment, the effect prevails postnatally and improves mother-infant interaction.
The decrease in the depressive symptoms remains in the intervention group 4 to 5 months old.The mothers in the intervention group will have a stronger attachment to their infant when the child is 4 to 5 months old.The quality of mother-infant interaction will be higher in the intervention group than in the control group when the child is 4 to 5 months old.

Moreover, we will explore the effect of the intervention on various forms of maternal psychological distress. However, too little is known about the trajectories of pregnancy-related anxiety in low-risk populations to state a hypothesis about this. For perinatal outcomes such as preterm birth (< 37 gestational weeks, [gwks]), intrauterine growth restriction (IUGR), and low (< 2.5 kg) birth weight at delivery, the power of the sample is likely to be too low to gain significant differences between groups.

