### Sample size {14}

The study aims to compare changes in EPDS scores between two independent groups. A mean decrease of three points in the EPDS score is considered clinically relevant and used for power calculations. A standard deviation (SD) of 3.5 points in the EPDS score used in power calculations was based on earlier studies in the Finnish population showing an SD of 3.7–4 [25]. A power analysis using a statistical power of 80% and a significance level of 0.05 (two-tailed) showed that 50 subjects are needed in both groups. Because of an estimated attrition rate of 10%, 60 subjects for both groups are currently being enrolled. Randomization was performed with random permuted blocks, using block size 10. The SAS® was used to generate the randomization (Version 9.4 for Windows).

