## Statistical methods

### Statistical methods for primary and secondary outcomes {20a}

The categorical variables of the study are characterized using frequencies and percentages. Continuous variables with means and SDs or medians with ranges and/or 25th and 75th percentiles are used. Age is summarized with the mean and the range.

If the assumptions for parametric analyses are met, the mean change of the EPDS score over time is analyzed using a linear mixed modeling approach for repeated measures. Then, the time point is considered as a within-factor and the treatment intervention as a between factor-effect. The effects of the participants’ background variables’ parity, age, antidepressant medication, care contacts within healthcare, and so forth, are also tested. The time point x intervention interaction describes whether the mean changes over time differ between the groups. The covariance structure of the unstructured (UN) and the compound symmetry (CS) is tested. The differences (together with 95% confidence interval [CI]) between the groups are also estimated at each time point, as well as within-group changes. Transformation for the EPDS or for other outcomes can be performed before analyses, if needed. The assumptions of parametric tests are checked using studentized residuals for justification of the analyses. Other numerical variables, mean change of MAAS, MPAS, SCL-90, and PRAQ-R2 score over time, are analyzed in a similar way.

*P*-values less than 0.05 are considered statistically significant (two-tailed). Statistical analyses are performed using SAS System for Windows, Version 9.4 or later (SAS Institute Inc., Cary, NC, USA).

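### Depression, attachment and representations are all called primary, with no success rule and one unadjusted 0.05 level; only the EPDS was sized, and the placing of the postnatal attachment scale is contradictory

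*Protocol article*

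**What the plan says.** - **Outcomes {12}** speaks of one primary outcome but lists three: the change in mean EPDS score "from before the intervention to after the intervention, maternal attachment, and prenatal representations before and after the intervention". It makes mother-infant relationship outcomes secondary.
- **Abstract, Methods** uses the plural: "The primary outcomes are a decrease in perinatal depressive symptoms assessed with EPDS and an increase in maternal attachment". Attachment is then measured by the WMCI, "the Maternal Antenatal Attachment Scale (MAAS), and the Maternal Postnatal Attachment Scale (MPAS").
- **Objectives {7}** puts attachment to the infant at 4 to 5 months under a second hypothesis, which opens: "If the intervention decreases prenatal depressive symptoms and improves prenatal attachment, the effect prevails postnatally and improves mother-infant interaction".
- **Sample size {14}** concerns the EPDS alone: "The study aims to compare changes in EPDS scores between two independent groups", and "A mean decrease of three points in the EPDS score is considered clinically relevant and used for power calculations".
- **Statistical methods {20a}** models EPDS change over time, then adds: "Other numerical variables, mean change of MAAS, MPAS, SCL-90, and PRAQ-R2 score over time, are analyzed in a similar way". The only significance rule is a general one on P-values: those "less than 0.05 are considered statistically significant (two-tailed"). The section gives no order of testing and no split of the level, and it names no test for the WMCI categories.

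**The concern.** The article does not settle what a positive trial is. There are three primary measures by the Outcomes section (EPDS, prenatal attachment on the MAAS, WMCI representations) and four by the abstract (adding the MPAS). Nothing says whether one success is enough or all are required, and each reading has a cost:

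- If one is enough, a significant result on any measure could be reported as meeting the primary outcome, and the overall error rate is above 5%.
- If all are required, the stated 80% power, worked out for the EPDS alone, is not the power of the primary objective.

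The MPAS contradiction makes even the number of primary tests uncertain.

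**Working it through.** **Inputs.** Number of primary measures: k = 3 (Outcomes {12}) or k = 4 (abstract). Level: 0.05 two-sided for each (Statistical methods {20a}). The correlation between the test statistics is not given, so I assume a common value and show 0 to 0.8.

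**1. The plan's own figure.** For a difference of 3, SD 3.5, two-sided 0.05 and 80% power:

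n per group = 2 × (1.960 + 0.842)² × 3.5² / 3² = 21.4, so 22 (23 with the t-distribution).

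The stated 50 per group is not reproduced. That is a separate matter, but it affects step 5.

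**2. Any one success counts, independent tests.** Chance of at least one false positive = 1 − 0.95^k.

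- k = 3: 1 − 0.8574 = 14.3%
- k = 4: 1 − 0.8145 = 18.5%

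**3. Any one success counts, correlated tests.** Equicorrelated normal statistics, by numerical integration:

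| Assumed correlation | k = 3 | k = 4 |
|---|---|---|
| 0 | 14.3% | 18.5% |
| 0.3 | 13.6% | 17.4% |
| 0.5 | 12.5% | 15.6% |
| 0.8 | 9.8% | 11.4% |

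Counting only false results that favour the intervention, under independence: 1 − 0.975³ = 7.3% and 1 − 0.975⁴ = 9.6%, against 2.5% for one test.

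**4. All must succeed.** Overall error is at most 5%. Joint power cannot exceed that of the weakest measure, and no power is given for the MAAS, MPAS or WMCI. As an illustration only, if each had 80% power and the tests were independent, joint power would be 0.8³ = 51% for three or 0.8⁴ = 41% for four.

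**5. What splitting the level would cost the EPDS.** Bonferroni gives 0.05/3 = 0.0167 (critical value 2.394) or 0.05/4 = 0.0125 (2.498). With 50 per group, power = Φ(difference / (SD × √(2/50)) − critical value).

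- Difference 3, SD 3.5: 3 / (3.5 × 0.2) = 4.286, so power is 97% (three) or 96% (four).
- Difference 3, SD 4 (top of the range cited in Sample size {14}): 3 / 0.8 = 3.75, so 91% or 89%.
- If 50 per group is instead taken to give exactly 80% at 0.05, the first term is 1.960 + 0.842 = 2.802. Power is then Φ(0.408) = 66% or Φ(0.304) = 62%. Restoring 80% needs (2.394 + 0.842)² / 2.802² = 1.33 times the sample, about 67 per group, or (2.498 + 0.842)² / 2.802² = 1.42 times, about 71.

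The cost of splitting therefore cannot be judged until the basis of the 50 is clear.

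**The case against.** The strongest defence is that a multiplicity procedure is commonly left to the analysis plan, which is not shown, so silence about order or adjustment is no defect. That is right as far as the procedure goes. It does not cover the choice of primary outcome. The article gives that its own section, lists several measures under a singular heading, and disagrees with its abstract about one of them.

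Three stronger readings are tempting and should be resisted.

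- *The false-positive rate is 13% to 19%.* A reader might infer this as a plain fact. It holds only if any single success counts, which no section says, and only for correlations up to about 0.5. Three of the measures concern maternal attachment, and the Background reports that depression and attachment are associated, so higher correlation is possible. The figure also includes false results against the intervention. The 18.5% end needs the MPAS as a fourth primary, which rests on the abstract alone.
- *The analysis breaks a gatekeeping rule in the Objectives.* The conditional sentence there can be read simply as a hypothesis that the effect persists. It sets no testing order, and it does not rank the EPDS before the MAAS or the MAAS before the WMCI.
- *Every primary measure has its own planned test at 0.05.* For the WMCI this rests only on the general P-value sentence, since no test is named.

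It is also fair to object that demoting attachment is not the only remedy. The stated aim is to reduce depression through attachment, and Holm or Bonferroni would keep it primary.

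**Conclusion.** The point stands in conditional form. The article names three primary measures in one section and four in another, sizes one, and gives a single unadjusted two-sided 0.05 with no success rule.

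On the any-one reading, error is roughly two to nearly four times nominal over the range examined (9.8% to 18.5% against 5%). Strong correlation reduces the excess but does not remove it. On the all-required reading the error is controlled, but the primary objective has no stated power. The figures rest on the assumed common correlation and on counting three or four tests. The contradiction over the MPAS needs no assumption.

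**What to change.** Before any outcome analysis:

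1. Name one primary outcome: the between-group difference in EPDS change from the first to the second interview, tested at two-sided 0.05. It is the only outcome sized. Identify it as that specific contrast from the mixed model, because the EPDS is also collected postnatally and the time-by-intervention interaction would otherwise span three time points.
2. Make the MAAS and WMCI (balanced against non-balanced) key secondaries, tested in a fixed order stated in advance and stopping at the first non-significant result. Name the test for the WMCI. The order is a choice for the trial team.
3. Alternatively, keep these measures co-primary, state that any one suffices, apply Holm or Bonferroni, and restate the EPDS power at the reduced level once the basis of the 50 per group is settled.
4. Place the MPAS in the postnatal secondary tier in the abstract, Objectives and Outcomes alike.

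**Cost.** Under the first option, attachment results lose confirmatory status if the EPDS is not significant. Under the alternative, EPDS power falls by an amount that depends on step 5 of the working. No extra participants are needed for the first option. Either way this is more than a wording change: the Trial section reports 66 women already recruited by December 7, 2021, and the section on protocol amendments {25} requires Ethics Committee acceptance before a change takes effect.

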### Participant timeline {13}

The participant timeline is described in Appendix 1. which is a research chart.

### Sample size {14}

The study aims to compare changes in EPDS scores between two independent groups. A mean decrease of three points in the EPDS score is considered clinically relevant and used for power calculations. A standard deviation (SD) of 3.5 points in the EPDS score used in power calculations was based on earlier studies in the Finnish population showing an SD of 3.7–4 [25]. A power analysis using a statistical power of 80% and a significance level of 0.05 (two-tailed) showed that 50 subjects are needed in both groups. Because of an estimated attrition rate of 10%, 60 subjects for both groups are currently being enrolled. Randomization was performed with random permuted blocks, using block size 10. The SAS® was used to generate the randomization (Version 9.4 for Windows).

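### The stated sample-size inputs do not give 50 women per group under either reading of the SD (23, or at most 44), and the abstract's 100 recruited conflicts with 60 per group enrolled

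*Protocol article*

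**What the plan says.** All inputs stand in Sample size {14} of the protocol article.

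- Comparison: "The study aims to compare changes in EPDS scores between two independent groups".
- Effect: "A mean decrease of three points in the EPDS score is considered clinically relevant and used for power calculations".
- SD: "A standard deviation (SD) of 3.5 points in the EPDS score used in power calculations", which, the sentence continues, "was based on earlier studies in the Finnish population showing an SD of 3.7–4".
- Error rates: 80% power and a two-tailed 0.05 level.
- Result: the analysis "showed that 50 subjects are needed in both groups".
- Attrition: "Because of an estimated attrition rate of 10%, 60 subjects for both groups are currently being enrolled".
- Randomisation: permuted blocks of 10, stated in the same section and again under Sequence generation {16a}.

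The Methods part of the abstract gives a different total. It begins "Altogether, 100 women scoring 10–15 on Edinburgh Pre-/Postnatal Depression Scale (EPDS", says that these women are recruited, and assigns half of them to the intervention. The section headed Trial reports 66 participants recruited by December 7, 2021, with recruitment still to be completed.

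**The concern.** The section supplies everything needed to recompute the number, and the recomputed number is well short of 50. The effect, SD, power and group size therefore cannot all be as stated, and a reader cannot tell which between-group difference the trial was designed to find. That matters most if the result is null, because the sample size section is where a reader learns what size of benefit the trial could have detected.

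The total is also stated in two ways. Recruitment was still open at the date of the article, so whether it stops at 100 or at 120 is a practical question.

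**Working it through.** **Is 50 a per-group figure?** Yes. The abstract puts half of 100 women in the intervention group. The 60 must also be per group, because 66 women had already been recruited and recruitment was continuing. The enrolment target is therefore 2 × 60 = 120.

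**Formula.** For two independent groups, n per group ≈ 2 × (1.960 + 0.842)² × SD² / Δ² = 2 × 7.849 × SD² / Δ². The exact t-test adds about one woman per group. Results marked t come from the noncentral t distribution.

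**Attempt to reproduce 50 with Δ = 3 and SD = 3.5**

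1. *3.5 is the SD of the change.* 2 × 7.849 × 12.25 / 9 = 21.4; t: 22.4, so **23 per group**.
2. *3.5 is the SD of a single score.* The SD of the change is then 3.5 × √(2(1 − r)), where r is the before-after correlation and the variances are taken as equal. The largest value for a non-negative r is at r = 0: 3.5 × √2 = 4.95. This gives 2 × 7.849 × 24.5 / 9 = 42.7; t: 43.7, so **44 per group**. Any positive r lowers it, and r = 0.5 returns to 23.
3. *What would be needed.* Fifty per group for 3 points requires a change SD of about 5.3. With a score SD of 3.5 this means r = 1 − 5.30² / (2 × 3.5²) ≈ −0.15.

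**Other variants at SD 3.5 and 3 points**

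| Variant | n per group |
|---|---|
| One-sided 0.05 | 18 |
| 90% power | 30 |
| 95% power | 37 |
| Bonferroni for four outcomes (normal approximation) | 31 |
| Wilcoxon test, worst case | 26 |
| Paired, within one group | 13 |

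None reaches 50.

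**Changing an input instead** (t-test, 80% power, two-sided 0.05)

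| SD | 3 points, SD of change | 3 points, score SD with r = 0 | 2 points, SD of change |
|---|---|---|---|
| 3.5 | 23 | 44 | 50 |
| 3.7 | 25 | 49 | 55 |
| 4.0 | 29 | 57 | 64 |

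Two points at SD 3.5 gives 49.05, so exactly 50. A score SD of 3.7 with zero correlation gives 49, which is close. Each replaces a stated input, and the second also adds an unstated zero correlation.

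**Power with 50 analysable women per group**

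| SD | 3 points, SD of change | 2 points, SD of change | 3 points, score SD with r = 0 |
|---|---|---|---|
| 3.5 | 98.9% | 80.8% | 85% |
| 3.7 | 98.0% | 76.3% | 81% |
| 4.0 | 96.0% | 69.7% | 75% |

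**Attrition.** 50 / 0.9 = 55.6, so 56 per group or 112 in total. The first multiple of 10 at or above 112 is 120, which is 60 per group.

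**Total.** 2 × 60 = 120 against the abstract's 100. If 100 were the number enrolled, 10% loss would leave 100 × 0.9 / 2 = 45 per group, five short of the stated 50.

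**The case against.** Several objections have force.

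- *The SD may be that of a score.* The text calls it an SD of points in the EPDS score. A reader who finds 23 against 50 might infer that the trial really has about 99% power for 3 points. The document does not support that. The figure treats 3.5 as the SD of the change, which for a score SD of 3.5 means a before-after correlation of 0.5. At zero correlation the power is 85%, or 75% at SD 4.0. This objection stands against any single power claim, but it does not rescue 50, because the ceiling at SD 3.5 is 44.
- *The true target may have been 2 points.* The exact match is suggestive, and a 3-point fall set against a 1-point fall in controls would produce it. But no control-group fall and no 2-point target is stated, and any standardised difference near 0.57 gives 50. It is a possible explanation only.
- *The SD of 3.5 below a cited range of 3.7 to 4 need not be an error.* The cited values come from the Finnish population, whereas this trial admits only women scoring 10 to 15. Such a restriction can plausibly reduce the spread. What remains is that no reason is given.
- *Sixty per group might be read as a wrong attrition step,* since on its own it corresponds to 16.7% loss (1 − 50/60). Rounding up to complete blocks of 10 explains it. The text does not say so, but there is no contradiction.
- *The abstract's 100 may be the evaluable number,* because it equals 2 × 50. That is likely enough, but the abstract says these women are recruited. The fall to 45 per group arises only if the 60 per group in the sample size section is not followed.

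**Conclusion.** The concern holds on two counts.

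1. The stated inputs do not yield 50 per group. They give 23 if 3.5 is the SD of the change, and no more than 44 if it is a score SD with equal variances and a non-negative before-after correlation. At least one input is misreported, and the article does not show which.
2. The abstract's 100 recruited and the 120 implied by 60 per group cannot both be the enrolment figure.

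The SD below its cited range and the step from 56 to 60 are secondary. Each has a plausible explanation that should be written down.

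It does not follow that the trial is underpowered. On the literal inputs 50 per group is more than is needed. Nor does it follow that enrolment should be cut to 23 per group, since the error may lie in the reported effect or SD. If the inputs actually used were less favourable, power could be well below 99%: 81% to 70% for 2 points with a change SD of 3.5 to 4.0, or 85% to 75% for 3 points with a score SD of 3.5 to 4.0 and no correlation. The analysis in section {20a} is unaffected.

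**What to change.** Leave enrolment as it is and restate the calculation in Sample size {14} from the inputs actually used:

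- the between-group difference in EPDS change that was targeted;
- whether the SD is that of the score or of the change, with the assumed before-after correlation if it is that of the score;
- why 3.5 was chosen when the cited studies show 3.7 to 4;
- the resulting power for 50 analysable women per group, shown across SD 3.5 to 4.0. The power table above gives these values for a change SD, and for a score SD with zero correlation.

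The authors should take the target difference and the type of SD from their own records. They should not adopt 2 points, or declare 3.5 a change SD, merely because the arithmetic then fits.

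State one enrolment target throughout: 120, that is 60 per group, with 10% attrition rounded up to complete blocks of 10 if that was the reasoning. A total of 112 would leave a block incomplete. In the abstract, correct 100 to 120 or label it as the evaluable number.

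The cost is a few sentences in the sample size section and the abstract. It needs no further participants and no change to the design. The stated power may turn out less favourable once the SD range is shown.
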